### Randomization and allocation concealment

The patients will be divided into five groups: a traditional acupuncture group (group A), a shallow-puncture group (group B), a non-acupoint acupuncture group (group C), a non-acupoint shallow-puncture group (group D) and a sham-puncture group (group E). Before randomization, all participants will be informed that they will be allocated into one of the above groups in an equal ratio, using block randomization with a block size of 5, and 35 participants are planned for each group. Randomization will occur on the second visit to the clinical research center according to the sequence generated by PEMS (Package for Encyclopedia of Medical Statistics) 3.1 software (West China School of Public Health, Sichuan, China) and overseen by an independent statistician. Randomization information will be sealed in opaque envelopes. If participants pass the screening test, a random number will be assigned sequentially.

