### Outcome measurements

#### Primary outcome measurement

##### Neck Pain Scale

The Northwick Park Neck Pain Questionnaire (NPQ) has been widely used in research and has been shown to have high validity and reliability for neck pain measurement [22]. It is comprised of nine items including the degree and duration of pain, symptoms including numbness, sleep and social activities, and quality of life aspects. The highest score is 100 and high scores indicate severe damage due to neck pain. The NPQ will be completed after each treatment and in the follow-up period.

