#### Sample size calculation

Following an academic literature review, a pilot study on acupuncture and its analgesic effect in CNP was identified [26]. The NPQ will be used as the primary outcome measure in assessment of the analgesic effect of acupuncture in this trial. Results from the pilot study with a two-arm design showed that the mean changes in NPQ were 20.71 ± 11.91 (acupuncture group) and 24.04 ± 11.83 (control group) [26]. However, our trial is a five-arm parallel-group study with the aim of assessing the efficacy of acupuncture. The mean ± standard deviation (SD) values reported in the pilot study will be used as the expected values in the treatment group and four control groups in the present study. PEMS 3.1 software was used to perform the sample size calculation. Thus, we calculated the appropriate trial sample size with 90% power, and the significance level was 0.05. The results showed that a clinically important difference was detected using a minimum sample size of 30 individuals in each group. With a maximum allowable dropout rate of 15%, a total of 175 subjects (35 per group) are being recruited.

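### The pilot figures the protocol plans on give about 19% power at 30 per group, not 90%, and as labelled they may point away from acupuncture

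*Protocol article*

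**What the plan says.** Under Sample size calculation, the protocol article reports from a two-arm pilot that "the mean changes in NPQ were 20.71 ± 11.91 (acupuncture group) and 24.04 ± 11.83 (control group". It says these means and SDs "will be used as the expected values in the treatment group and four control groups in the present study". It continues: "we calculated the appropriate trial sample size with 90% power, and the significance level was 0.05". The conclusion is: "The results showed that a clinically important difference was detected using a minimum sample size of 30 individuals in each group". Allowance for loss follows: "With a maximum allowable dropout rate of 15%, a total of 175 subjects (35 per group) are being recruited".

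The section names no test, sidedness, contrast or multiplicity adjustment, and no target difference other than the one implied by the pilot means. On the scale itself, the Neck Pain Scale section says: "The highest score is 100 and high scores indicate severe damage due to neck pain". The Statistical analysis section compares mean differences from baseline between groups by ANOVA.

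**The concern.** Everything needed to repeat the calculation is on the page: means, SDs, power, significance level and result. A difference of a little over 3 points against an SD of nearly 12 is a small effect, and 30 per group is a size that suits a large one.

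Three things are wrong with the passage.

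- **The number.** The stated power does not follow from the stated inputs.
- **The direction.** The pilot figures are labelled changes. If they are improvements, control improved more than acupuncture, and the planning alternative runs against the trial's hypothesis. If they are post-treatment scores, the lower acupuncture value favours acupuncture, but then they are not changes, whereas the planned analysis is of changes.
- **The label of clinical importance.** The only difference available is 3.33 points on a scale whose highest score is 100, and no basis is given for calling it clinically important.

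The trial asks whether acupuncture beats placebo and which sham is the best control. If the planning difference is true, a non-significant result is by far the likeliest outcome. A reader who trusts the 90% figure would take that result as good evidence that acupuncture is no better than sham, or that the sham arms are interchangeable.

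**Working it through.** **Inputs** (Sample size calculation, unless noted)

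- Group A mean 20.71, SD 11.91; each of the four control groups mean 24.04, SD 11.83.
- Power 90%, significance level 0.05. Two-sided is assumed; one-sided was also tried.
- Equal allocation (Randomization and allocation concealment: "they will be allocated into one of the above groups in an equal ratio").
- Stated result: 30 per group, raised to 35.

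**Effect size**

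- Difference = 24.04 − 20.71 = 3.33.
- Common SD = √[(11.91² + 11.83²)/2] = √[(141.85 + 139.95)/2] = 11.87.
- d = 3.33/11.87 = 0.2805.

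**Attempt to reproduce 30 per group**

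Pairwise, normal approximation: n = 2 × (1.960 + 1.282)² / 0.2805² ≈ 267.0, rounded up to 268. The exact noncentral t calculation also gives 268. Five arms make 5 × 268 = 1,340 evaluable patients.

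Five-group ANOVA: the grand mean is (20.71 + 4 × 24.04)/5 = 23.374. The squared deviations sum to 2.664² + 4 × 0.666² = 8.871, so f = √(8.871/5)/11.87 = 0.112. At n = 30 the noncentrality is 30 × 8.871/11.87² = 1.89. The noncentral F gives 90% power first at 246 per group, or 5 × 246 = 1,230 in total.

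Results by reading (noncentral t or F throughout):

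| Reading | Power at 30 per group | n per group for 90% |
|---|---|---|
| Pairwise, two-sided 0.05 | 18.8% (21.2% at 35) | 268 |
| Pairwise, one-sided 0.05 | 28.4% | 219 |
| Five-group ANOVA | 16.0% (18.2% at 35) | 246 |
| A v pooled controls, two-sided | 27.6% | 168 |
| A v pooled controls, one-sided | 39.1% | 137 |

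None gives 30. The smallest requirement, 137, is about 4.5 times the stated number. A Bonferroni adjustment for four comparisons (0.0125, which the protocol does not specify) would lower pairwise power to 7.5%.

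**What 30 per group does deliver** (two arms, SD 11.87, two-sided 0.05)

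- Difference detectable with 90% power: 0.851 × 11.87 ≈ 10.1 points, three times the pilot difference. The ANOVA equivalent, with one arm differing from the other four, is about 9.7 points.
- SD at which 3.33 points would be detectable with 90% power: 3.33/0.851 ≈ 3.9, against the stated 11.9.
- Expected 95% CI half-width: 2.002 × 11.87 × √(2/30) ≈ 6.1 points, nearly twice the planning difference.

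The dropout step is close: 30/0.85 = 35.3, which rounds up to 36 where the protocol has 35. That is immaterial beside the rest.

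**The case against.** The strongest reply is that a journal article condenses the calculation. The section names no test, sidedness or contrast, so no single power figure can be pinned on it, and the full protocol may hold a separate target difference. The first part is fair, and the power is best read as a range: 16% to 39% across the readings that use only the stated 0.05. The second part does not rescue the text, which says the pilot values are the expected values. If another difference was used, that statement is wrong.

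Baseline adjustment does not close the gap. Bringing an SD of 11.87 down to 3.9 would need a correlation of about 0.94, and the stated analysis is ANOVA on differences from baseline, with no covariate.

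On direction, it is true that the document cannot settle whether the pilot figures are improvements or final scores, and that the sign does not alter a two-sided sample size. So the point is conditional; what is certain is that the label must be clarified. It is also true that the protocol does not itself attach 3.33 to the words about clinical importance. That link is an inference, though the natural one, since no other difference appears.

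Finally, a restated figure of about 10 points is for one unadjusted pair of arms, while group A faces four controls. This stands as a caution: the corrected sentence must name its assumptions. With the Bonferroni variant the detectable difference rises to about 11.9 points. Nothing in the protocol says a null would be read as equivalence, but a claim of 90% power invites that reading.

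**Conclusion.** The concern holds and the statement must be corrected. On the protocol's own inputs, 30 evaluable patients per group gives 18.8% power for a two-sided pairwise comparison at 0.05 and 16.0% for the five-group ANOVA. The chance of a non-significant result under the planning assumption is therefore about 81% or 84%. Ninety per cent power would need 268 or 246 per group.

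These figures assume a common SD of 11.87, equal groups, no multiplicity adjustment and, for the ANOVA, one arm at 20.71 and four at 24.04. Relaxing sidedness or pooling the controls raises power to 39% at most. The size of the shortfall is the same whether the pilot figures are changes or final scores. Which arm they favour is not, and the document leaves that open.

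**What to change.** Keep 175 patients and rewrite the sample size paragraph.

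1. State whether 20.71 and 24.04 are changes from baseline or post-treatment scores, and which direction is benefit.
2. Remove the claim that 30 per group detects a clinically important difference. If a difference other than 3.33 was the real target, give it with its justification.
3. Replace the power claim with wording such as: *With 30 evaluable patients per group, an SD of 11.9 and a two-sided 0.05 test between two arms, unadjusted for multiple comparisons, power is 90% for a difference of about 10 NPQ points and about 19% for 3.33 points. The expected 95% confidence interval half-width is about 6.1 points.* If the powered test is to be the five-group ANOVA, quote its figures in place of these (about 9.7 points and 16%). If the four comparisons with group A are to be adjusted, recompute.
4. State that a non-significant result will be reported with its confidence interval and will not be read as equivalence, either of acupuncture and sham or of one sham with another.

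The cost is protocol wording only, with no added patients. The price is a much less favourable power statement, and 3.33 points stays out of reach at this size. Holding 90% power for that difference would instead take 268/0.85, or 316 per group after dropout (5 × 316 = 1,580 in all).

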#### Statistical analysis

A statistical analysis will be performed using the Statistical Package for Social Sciences (SPSS, version 16.0, SPSS Inc., Chicago, IL, USA) in the Center of Acupuncture Clinical Research. A full analysis set (FAS) will be performed as the main analysis. According to the principle of intention-to-treat (ITT), any participants who randomly receive at least one treatment should be included in the main analysis dataset. The per-protocol (PP) set as the subset of FAS will include subjects who complete the study and have main variable baseline values in this trial. To be included in the safety set, patients will receive at least one safety evaluation after treatment. Statistical analysis of the main parameters will be carried out at baseline, at each visit and in the follow-up period. Frequency tables and charts will be used to analyze completed AE questionnaires.

Descriptive statistics will be performed to compare baseline information, patient characteristics and an evaluation of the credibility of the five groups. To determine the primary and secondary outcomes, the mean differences from baseline to the end of follow-up period will be compared and analyzed. Group differences for continuous variables will be analyzed using analysis of variance (ANOVA) to compare the subjective and semi-objective outcomes. The Wilcoxon rank sum test will be used to compare the outcome measurements before and after treatment. The differences in categorical variables between groups and adverse effects will be analyzed using the chi-square test. A *P* value of 0.05 or less will be considered significant.

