### Blinding

All patients will be treated in the acupuncture clinical research center and will not be informed of the type of treatment that they will receive. Outcome assessors, data managers and the statistician will be blinded in this trial. To preserve masking, only the acupuncturists will have access to treatment allocation [19, 20]. However, they must learn how to use the blinding method to communicate with participants to ensure treatment blinding. The blinding principle will be operated until the data are locked down. The questionnaires regarding blinding will be completed immediately after the 5th and 10th treatments, as well as at the end of the follow-up. The success of these blinding strategies will be appraised at the end of the study by the Blinding Index (BI).

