### Interventions

Participants will be randomized to the five treatment groups and receive ten sessions of treatment over a period of 5 weeks. Acupuncture treatment will be performed by a senior acupuncturist who has held a practitioner licence for more than 10 years. The participants will be asked to rest for 15 min before treatment. A constant room temperature of 23 to 25 °C will be maintained to ensure the patients are comfortable and relaxed during treatment. Subjects will be advised to lie in the prone position on the treatment couch. Interventions will be performed twice a week from Monday to Friday. Each session will last for 20 min.

The combinations of EX-HN 15 and SI 15 will be selected for the different groups based on the academic literature [21]. EX-HN 15 is an acupoint on the neck, 2 cun (1 cun is equal to the width of the patient’s thumb knuckle stripe) above GV 14 (*Dazhui*), and 1 cun lateral to the posterior median line. SI 15 is located on the back, under the 7th cervical vertebra and 2 cun lateral to GV 14. According to TCM theory, stimulation of EX-HN 15 and SI 15 can remove meridian stasis by promoting the circulation of “Qi” and blood to relieve neck pain. After the skin is sterilized with disposable 75% alcohol swabs, a sterile needle (length: 25 mm, diameter: 0.30 mm; Huatuo, Suzhou Medical Supply Factory Co., Ltd., Suzhou, China) will be inserted. The needle-punching depth in the acupoint will be 0.5 to 0.8 cun. The needle will be manipulated by lifting and twirling until the participant feels a sensation (denominated *de-qi*).

The needle in the non-acupoint will be inserted without the use of acupuncture techniques during the experiments. Non-acupoints 1 and 2 are located 1 cm lateral to EX-HN 15 and SI 15. The shallow puncture is just enough to maintain the needles in a fixed position and not enough to produce *de-qi*. For subjects receiving sham puncture, “Streitberger” needles (Asiamed Inc., Bridport, UK) with blunt tips will be used in the same areas as those in the treatment group, but will not pierce the skin. The needles will then be fixed and retained for 20 min. The treatment details in each group are illustrated in Table 1.

**Table 1 Tab1:** Treatment details of each group

Group	Acupoint	Manipulation
Group A traditional acupuncture	EX-HN 15 (*Jingbailao*)	The needle-punching depth in the each acupoint is 0.5 to 0.8 cun. The sensation (denominated *de-qi*) is necessary
	SI 15 (*Jianzhongshu*)	

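### The main analysis is described as intention-to-treat but admits only patients who receive at least one treatment, and no defined set contains all randomised patients

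*Protocol article*

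**What the plan says.** All references are to the protocol article.

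- **Main set.** Statistical analysis states: "A full analysis set (FAS) will be performed as the main analysis". The entry rule follows directly, under an appeal to the intention-to-treat principle: "any participants who randomly receive at least one treatment should be included in the main analysis dataset".
- **Other sets.** "The per-protocol (PP) set as the subset of FAS will include subjects who complete the study", and those subjects must also have baseline values of the main variable. The safety set requires a safety evaluation after treatment.
- **Timing.** Randomization and allocation concealment: "Randomization will occur on the second visit to the clinical research center". A random number is issued once screening is passed. Treatment follows.
- **Who knows the arm.** Blinding: "only the acupuncturists will have access to treatment allocation". Patients "will not be informed of the type of treatment that they will receive", and outcome assessors, data managers and the statistician are also blinded.
- **Who treats.** Interventions: "Acupuncture treatment will be performed by a senior acupuncturist".
- **Missing data.** Missing data and sensitivity analysis names LOCF as the imputation method. It promises a sensitivity analysis across the datasets but does not name one made up of all randomised patients.

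**The concern.** Intention-to-treat keeps a patient because the patient was randomised. The rule here keeps a patient because treatment was received, which is an event after randomisation. The label and the definition therefore disagree, and the article has fixed the definition itself rather than leaving it to a later document.

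The usual defence of a treated-at-least-once set is that knowledge of the allocation cannot influence whether treatment starts. In a trial where the treating staff are masked, that is easy to accept. Here the person who delivers the first session knows the arm, so the independence has to be argued or checked, and the article does neither. At stake is whether a result reported as intention-to-treat compares the groups as randomised.

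**Working it through.** **Step 1: compare the definitions.** No stated figure needs reproducing, so the first check is one of set membership. Take a patient randomised at the second visit who never receives a session.

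| Set | Entry condition | Is this patient in it? |
|---|---|---|
| Main set (FAS) | at least one treatment | No |
| Per-protocol | subset of the FAS, completers | No |
| Safety | a safety evaluation after treatment | No |
| Sensitivity analysis | run across the sets above | No |

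As written, no analysis uses this patient.

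**Step 2: size of the possible shift.** The documents give neither the number of randomised but untreated patients nor how their outcomes would differ. Both are assumptions here. Let m patients out of 35 be left out of one arm, and let their mean NPQ change differ by g points from that of the patients kept. Then

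shift in the arm mean = (m / 35) × g.

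The planning difference, from Sample size calculation, is 24.04 − 20.71 = 3.33 points. The planning SDs are 11.91 and 11.83, so g = 12 is about one SD.

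| m | g = 5 | g = 10 | g = 12 |
|---|---|---|---|
| 1 | 0.14 (4%) | 0.29 (9%) | 0.34 (10%) |
| 3 | 0.43 (13%) | 0.86 (26%) | 1.03 (31%) |
| 5 | 0.71 (21%) | 1.43 (43%) | 1.71 (51%) |

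Percentages are of 3.33. The row m = 5 is an extreme: it is the whole 15% dropout allowance of one arm (0.15 × 35 = 5.25) lost before the first session. The bias in a comparison is near zero if nobody is lost at that stage or if losses do not depend on arm.

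**Step 3: what LOCF would do to these patients.** If they are brought back with only a baseline NPQ, carrying that value forward gives a change of zero. For an arm whose other patients have mean change μ, the arm mean falls by (m / 35) × μ:

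- m = 1: 20.71 / 35 = 0.59, or 24.04 / 35 = 0.69
- m = 3: 3 × 20.71 / 35 = 1.78, or 3 × 24.04 / 35 = 2.06

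The fall is therefore about 0.6 to 2.1 points, or 18% to 62% of 3.33, if all such patients are in one arm. If each of two compared arms has the same m, the planning difference only shrinks by (m / 35) × 3.33, which is 0.10 for m = 1 and 0.29 for m = 3.

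For 1 to 3 patients in one arm, the choice of imputation can move the arm mean by more than the shifts in Step 2. The remedy has to take account of that.

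**The case against.** The strongest reply is that the wording is loose rather than harmful. The main set is named a full analysis set. The sentence says who should be included and has no explicit exclusion clause, and its English is awkward. Patients do not know their arm, which limits refusals related to arm. Reasons for quitting are recorded at any time under Data monitoring and quality control, and the dropout rate is to be analysed.

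Much of this stands, and it keeps the point minor. It does not remove it. The natural reading is still randomised and treated at least once, and if all randomised patients were meant, the sentence needs correcting anyway. Recording reasons for dropout does not put the patients into an analysis.

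A reader might infer three stronger things that the documents do not support:

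- **That acupuncturists decide, knowing the arm, whether a patient is started, deferred or found unsuitable.** No section gives them that decision. Enrolment belongs to recruitment staff, judgements about unsuitable medication belong to the recruitment investigators, and the random number is issued only after screening is passed. The article does not say who opens the envelopes. Knowledge of the allocation makes arm-related loss possible; it does not show that the plan provides for it.
- **That the first session is the only point at which an unmasked person acts.** Acupuncturists deliver all ten sessions.
- **That patients might be analysed in an arm other than the one assigned.** The appeal to intention-to-treat covers this, and nothing in the text suggests analysis by treatment received.

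**Conclusion.** The point holds as a minor one. The article claims the intention-to-treat principle for a set that depends on receiving treatment, and none of its defined sets restores the randomised but untreated patients. Because the treating acupuncturists know the allocation, the plan cannot simply assume that starting treatment is independent of arm. It does not follow that such dependence exists or is likely.

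The effect is probably small: 0.14 to 1.03 NPQ points on one arm's mean (4% to 31% of the planning difference) for 1 to 3 losses from that arm and a gap of 5 to 12 points. Both inputs are assumed, and the effect is zero if everyone randomised has a first session.

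**What to change.** **Preferred.** Define the main set as all randomised patients, analysed in the arm allocated, and keep the treated-at-least-once set as a sensitivity analysis.

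**Minimum.** Call the current set modified intention-to-treat and add a sensitivity analysis of all randomised patients.

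**In either case:**

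- Report the number of randomised but untreated patients by arm, with reasons. The CRF already records reasons for quitting.
- Where possible, collect follow-up NPQ from these patients through the telephone and message contacts already planned, so that fewer depend on imputation.
- Show the all-randomised result under at least one method other than LOCF, for example multiple imputation, or a repeated-measures model that treats the baseline as one of the outcomes so that patients with only a baseline value are retained.

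**Cost.** A sentence or two of wording and one further analysis. The drawback is that patients with only a baseline NPQ depend on the missing-data method. LOCF would assign them no change, which is why the result should not rest on LOCF alone.

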**Methods/design:**

A five-arm, parallel, single-blinded, randomized, sham-controlled trial was designed. Patients with CNP of more than 3 months’ duration are being recruited from Guangdong Provincial Hospital of Chinese Medicine (China). Following examination, 175 patients will be randomized into one of five groups (35 patients in each group) as follows: a traditional acupuncture group (group A), a shallow-puncture group (group B), a non-acupoint acupuncture group (group C), a non-acupoint shallow-puncture group (group D) and a sham-puncture group (group E). The interventions will last for 20 min and will be carried out twice a week for 5 weeks. The primary outcome will be evaluated by changes in the Northwick Park Neck Pain Questionnaire (NPQ). Secondary outcomes will be measured by the pain threshold, the Short Form McGill Pain Questionnaire-2 (SF-MPQ-2), the 36-Item Short-Form Health Survey (SF-36) and diary entries. Analysis of the data will be performed at baseline, at the end of the intervention and at 3 months’ follow-up. The safety of acupuncture will be evaluated at each treatment period.

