In view of these doubts, the influence of different needling points and depths should be investigated. First, the acupoints of local lesions including *Jingbailao* (EX-HN 15) and *Jianzhongshu* (SI 15) are commonly used in our hospital for neck pain [15]. The analgesic mechanism of acupoints on local lesions has been established in the spinal segments control theory to explain the gate control theory [16, 17]. According to the innervations of the pain focus, the effects of stimulation of EX-HN 15 and SI 15 on neck analgesia will be studied for feasibility and repeatability [15]. Second, several different groups of non-acupoints and shallow punctures will be established to determine whether traditional acupuncture is more effective for chronic pain relief than sham acupuncture in adults with CNP. The different depth and placement of needle insertion will also be investigated to determine efficacy [18]. Third, a single-blinded practice will be used and the adequacy of subject blinding will also be carefully assessed. The patients will be advised to lie in the prone position on the treatment couch and will be unaware of the treatment course in this trial. Data collection will be completed by the researchers over a 3-month follow-up period. Finally, we will assess the pain threshold (PT) and pain diary as semi-objective outcomes to avoid subjective results.

In this research, a randomized clinical trial will be performed to determine whether the outcome of traditional acupuncture treatment is significantly different to sham acupuncture in relieving CNP. We also aim to investigate which type of sham acupuncture is the optimal control for clinical trials.

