#### Secondary outcome measurement

##### Pain threshold

A patient’s pain threshold (PT) is a semi-objective outcome and will be measured twice after each treatment. The PT measuring device (EP601C, East China Normal University of Science and Technology, Guangxi, China) has a 5-mA range. The positive electrode (anode) of the device is placed in the area of pain, and the other electrode is placed on the leg. According to the staircase method, the stimulus selection procedure with an increasing sequence of current stimulation from 0 mA in 2-mA steps will be presented to the patient. The patient will control the switch and press the stop key once they feel pain. The current strength (mA) on the screen will be recorded and the sequence direction will then be reversed. The descending sequence will be stopped when the participant feels pain, and the sequence points will be reversed again [23]. Three measurements will be recorded and the average PT calculated for each patient. PT will be assessed before and after treatment and the mean value calculated after the 5th and 10th treatments.

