#### Follow-up

The researcher will contact the patients via telephone and a short messaging service. The follow-up period will be 3 months and monthly information will be collected. If participants discontinue the intervention protocols, the latest outcome data including changes in symptoms and medication compliance will be presented. The reasons for treatment failure will be recorded and analyzed.

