#### Missing data and sensitivity analysis

In order to obtain the complete dataset, the researchers will receive professional training to avoid missing data. Experienced investigators will contact participants through messaging and telephone calls at fixed treatment periods. In addition, the participants will receive economic compensation after the trial. For missing data, we will analyze the underlying reason and use an imputation adjustment approach. The method of last observation carried forward (LOCF) will be carried out for imputation of missing values. After the main analysis, sensitivity analysis of the various datasets will be used to evaluate the impact of missing data on the trial results.

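### The analysis compares all outcomes from baseline to the end of follow-up, but the text describes no pain-threshold reading after the treatment period

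*Protocol article*

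**What the plan says.** All places are in the protocol article.

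- **Statistical analysis** fixes the window: "To determine the primary and secondary outcomes, the mean differences from baseline to the end of follow-up period will be compared and analyzed". No outcome is exempted. Group differences in continuous variables are then "analyzed using analysis of variance (ANOVA) to compare the subjective and semi-objective outcomes".
- **Abstract** lists pain threshold first among the secondary outcomes and names 3 months' follow-up as an analysis time.
- **Background** explains its role: "we will assess the pain threshold (PT) and pain diary as semi-objective outcomes to avoid subjective results".
- **Pain threshold** gives the timing in two sentences. One says it "will be measured twice after each treatment". The other says: "PT will be assessed before and after treatment and the mean value calculated after the 5th and 10th treatments". The method needs one electrode at the painful area and one on the leg.
- **Follow-up**, which lasts 3 months with monthly collection, says: "The researcher will contact the patients via telephone and a short messaging service".
- **Missing data and sensitivity analysis** says, without limiting it to any outcome: "The method of last observation carried forward (LOCF) will be carried out for imputation of missing values".

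**The concern.** The analysis rule asks for a pain-threshold change at a time when, as far as the text goes, nobody measures it. The method cannot be carried out by telephone or message. The neighbouring outcomes do state a follow-up assessment, so the silence on pain threshold does not look like mere brevity.

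Pain threshold is the only outcome taken with a device; the diary, also called semi-objective, is filled in by the patient. A semi-objective 3-month result would carry weight in a trial whose participants' blinding is itself under test. If that result were an end-of-treatment value under a 3-month label, readers would take it as evidence of lasting benefit that was never observed.

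**Working it through.** No stated figure, such as a sample size or power, enters this point. The check sets the measurement schedule beside the analysis window.

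**Step 1. Is an end-of-follow-up assessment stated in the text?**

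| Outcome | Stated timing | Follow-up assessment stated? |
|---|---|---|
| NPQ (primary) | after each treatment and during follow-up | yes |
| SF-36 | before treatment, after sessions 5 and 10, end of follow-up | yes |
| Pain diary | baseline, after sessions 5 and 10, end of follow-up | yes |
| SF-MPQ-2 | none given; asks about the previous week | not stated, but a questionnaire can be given remotely |
| Pain threshold | around treatment; values after sessions 5 and 10 | no |

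**Step 2. Count the readings.** The Sample size calculation section plans 35 patients in each of five groups: 5 × 35 = 175. Pain-threshold readings described at the end of follow-up: 0 of 175, or 0 of 35 in every group.

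**Step 3. Apply the analysis rule literally.** There are two possible outcomes.

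- *Carry-forward is not applied to an unscheduled reading.* The baseline-to-end-of-follow-up comparison then has no pain-threshold data.
- *Carry-forward is applied.* All 175 values (175/175 = 100%) are imputed. Treatment completers carry a session-10 value from week 5, about 3 months (roughly 13 weeks) old. Patients who leave during treatment carry an older one. At the planned maximum dropout of 15%, that is at most 0.15 × 175 = 26.25, about 26 patients, and only if all of them leave before session 10.

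In the second case, write B for the baseline value and L for the last treatment-period value. The change labelled 3-month is L − B. The end-of-treatment change, imputed in the same way, is also L − B. The two comparisons are identical for every patient, so the 3-month one adds no information.

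**Step 4. Would the plan's safeguards catch this?** Staff training and reminder calls reduce missed visits, but this gap comes from the schedule and exists with no dropout at all. The sensitivity analysis across datasets cannot show it either, because neither the full analysis set nor the per-protocol set would hold a 3-month reading.

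**Step 5. Which reading is the last one?** The two timing sentences do not agree. One describes only post-treatment readings; the other describes readings before and after. The second can also mean before and after each session, or before and after the whole course. The mean value it mentions may combine pre- and post-session readings, or may be the average of the three staircase measurements described just above it. The text does not settle how far the summarised value reflects an immediate response to needling.

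**The case against.** The strongest reply has four parts.

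1. *The deciding evidence is missing.* Fig. 2 is the assessment schedule and is not shown, and the text is not a full schedule, since SF-MPQ-2 has no times at all. This stands as a limit. One cannot say that no reading is planned, only that none is described. If Fig. 2 lists one, it has to be squared with the Pain threshold and Follow-up sections.

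2. *Telephone contact does not exclude a visit.* This is correct. The Follow-up section does not say that contact is only remote, and the missing-data section uses similar wording for the treatment phase, when patients attend in person. A reader might infer that a 3-month reading is impossible under the plan; the text does not go that far. It describes no follow-up visit.

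3. *Carry-forward is meant for missing values, not unscheduled ones.* This also stands. A reader might infer that the plan intends to report the 10th-session reading as the 3-month result. The document does not say so, and the Statistical analysis section also mentions analysis at each visit, which allows pain threshold to be analysed when it was measured. But the sentence that fixes the outcome comparison makes no exception for pain threshold, and if carry-forward is not used, that comparison has no data.

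4. *The consequence is limited.* The NPQ is collected during follow-up, so the main answer is safe, and no section announces a durability claim from pain threshold. Both are true, and they limit the point to one secondary outcome.

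A further tempting claim is that a before-and-after average would pass exactly half of any immediate effect into the 3-month result. That requires the mean value to be a pre/post average, which the text leaves open.

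That a journal article condenses the full protocol does not remove the point: it rests on a conflict between sentences that are present, not on an omitted detail.

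**Conclusion.** The point holds as a conflict between the stated comparison window and the stated measurement schedule for pain threshold. On the text shown, 0 of 175 end-of-follow-up readings are described. The 3-month comparison is then either empty or, if the general carry-forward rule is applied, 100% imputed and identical to the end-of-treatment comparison. In neither case does it bear on durability.

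This assumes that Fig. 2 adds no follow-up reading and that no in-person follow-up visit takes place. If either assumption fails, the plan still needs correcting, because its sections would then disagree about when pain threshold is measured. The two timing sentences need reconciling in any event. The matter concerns a secondary outcome and leaves the primary analysis untouched. It should be corrected because the correction is cheap and the result it prevents would mislead.

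**What to change.** - **Statistical analysis:** define the pain-threshold comparison as change from baseline to the 10th treatment, with the 5th as support, and exclude pain threshold from the end-of-follow-up comparison.
- **Missing data and sensitivity analysis:** state that last observation carried forward does not extend pain threshold beyond its last scheduled reading.
- **Pain threshold:** reconcile the two timing sentences and say what the mean value averages. If pre-session readings are taken, use them for the endpoint and report the after-minus-before change separately as an immediate effect. If they are not taken, that refinement is not available.
- **Fig. 2:** check it against the text and correct whichever is wrong.
- **Conclusions at 3 months:** rest them on outcomes actually collected at follow-up, namely NPQ, SF-36, the diary, and SF-MPQ-2 if it is administered then.

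These are wording changes and need no new visit or measurement. The cost is giving up a device-measured claim at 3 months. If that claim is wanted, an in-person reading has to be scheduled, with the added burden of a visit.
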